**Figure 9: Study Three (RCT) Flow Chart**

### Control group (Standard care)

Patients will be directed to follow the standard care ACLR rehabilitation protocol from preoperative until 12 weeks after the ACLR (see Figure 10). Both study groups will receive standard physiotherapy care from the Department of Medical Rehabilitation Services (HCTM). For standard care rehabilitation sessions, there are five physiotherapists in charge with more than five years of clinical expertise in musculoskeletal rehabilitation. Current rehabilitation strategies consist of knee mobilisation exercises, cryotherapy, and progressive resistance exercises, including eccentric strengthening exercises, proprioceptive training, and dynamic stabilisation drills. The standard outpatient physiotherapy program takes about one hour per session, with a recommendation of 1-2 sessions per week until three months post-operative.

All participants are encouraged to diligently follow the designated daily home exercise program. The standard care involves a personalised therapeutic exercise programme that is specifically designed to meet the needs of each client's goal and the timeline of ACLR recovery. This physiotherapy outpatient rehabilitation program lasts approximately one hour per session, with 1-2 attended sessions per week recommended until three months post-operative. Furthermore, all participants are instructed to diligently adhere to the prescribed daily home exercise programme (see Appendix H).

### **Intervention Group (ULIT + Standard Care)**

A single physiotherapist will administer the ULIT. The treating physiotherapist will present the ULIT to patients in verbal, demonstration, and written formats. In the fourth week following ACLR surgery, the treating physiotherapist will conduct the ULIT as a single, personalised session. The treating physiotherapist will instruct patients to follow the ULIT from 4 to 12 weeks post-operatively together with the standard care ACLR rehabilitation protocol. The ULIT comprised three concise isometric exercises: 1) wall push-up, 2) shoulder extension, and 3) shoulder external rotation (see Appendix I). The intervention group will be instructed to continue the ULIT plus standard care rehabilitation daily as a warm-up and home exercise programme for eight weeks.

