## **Specific Objectives**

1. To investigate the difference in hamstring strength between the ULIT and the standard care group compared to the standard care alone group at 4, 8, and 12 weeks post-ACLR.
2. To measure the changes in physical function based on the IKDC score in the ULIT group compared to the standard care group at preoperative and 12 weeks post-ACLR.
3. To evaluate the effect of ULIT on hamstring flexibility, measured by the active knee extension test (AKET) test, compared to standard care alone at preoperative and 12 weeks post-ACLR.
4. To analyse the relationship between patient adherence to ULIT and improvements in hamstring strength and physical function over the 12-week rehabilitation period.

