## **Randomisation and Allocation**

Following the baseline assessments, individuals will be assigned either to the intervention group or the control group by a simple random sampling. The randomisation process will be performed using a computer-generated sequence numbering scheme ranging from one (1) to thirty-two (32), with an equal allocation ratio of 1:1. The concealment is achieved using a set of sealed and numbered envelopes. Allocation takes place following baseline testing (T1), when a staff of the Orthopaedic Department, who is not participating in the study, opens the next study envelope. Subsequently, they notify the group assignment to the attending physiotherapist. The envelopes will be securely stored and sealed in a cabinet to ensure security and prevent any unauthorised access. Measures will be implemented to restrict the number of authorised individuals who have access or authority to open the research envelopes, to prevent any potential bias in the allocation process. The statistical analysis will specifically focus on allocation codes, ensuring that the data analyzers remain unaware of the study group allocation (see Figure 9).

[figure not shown]

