### **Data Collection**

The study will collect demographic data, as well as pre-, intra-, and postoperative data (see Table 3). Data will be gathered from the participants and their medical records for all the data collection forms (see Appendix A, C, and D). Baseline evaluations will be conducted throughout the pre-operative period, within a range of 14 days, to reduce any bias when selecting participants. The subsequent assessment in the 4th week ( $\pm 14$  days), 8 weeks ( $\pm 14$  days), and three months ( $\pm 14$  days) are scheduled at the Orthopaedic Clinic (van Melick et al., 2021). The blinded assessors will give all tests and questionnaires in person, ensuring participant consistency. These assessments will take place at four weeks, eight weeks and three months after the surgery. Phone consultations will be used for post-hospital discharge follow-up. Participants who cannot be reached by phone for a continuous period of 14 days starting from the assessment due date will be classified as lost to follow-up for outcome measurement.

intra-reliability had a value of 0.9269 [95% C.I.: 0.8909–0.9533] (Grgic et al., 2020; Karagiannopoulos et al., 2022; Romero-Franco et al., 2019).

The participants are directed to generate deliberate isometric contractions of their quadriceps or hamstring muscles, by pushing against the resistance provided by the dynamometer's arm with a perceived maximal effort of 100% (Grgic et al., 2020). During the formal testing, the participants conducted three maximum voluntary isometric contractions (MVIC) of knee extension lasting five seconds each for the quadriceps (Padulo et al., 2020). Similarly, This is followed by knee flexion testing for the hamstrings. A minute rest time will be given between the quadriceps and hamstring testing (Mellemkjær et al., 2024).

The assessor will consistently give instruction and verbal encouragement (see Appendix I). The participants are instructed to exert maximum force by either pushing with their quadriceps or pulling with their hamstrings against the dynamometer. The average and best scores of the peak forces will be recorded (Grgic et al., 2020).

The average scores of quadriceps and hamstring muscular strength during rehabilitation are quantified using the Quadriceps Index (QI) and Hamstring Index (HI), which are calculated using the formula:  $(\text{MVIC peak force of the affected limb} / \text{MVIC peak force of the unaffected limb}) \times 100$  (van Melick et al., 2021).

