## Statistical Analysis

The data analysis will be conducted using the SPSS Windows Version 29.0 software (SPSS, Chicago, IL, USA). The data will be summarised using descriptive statistics such as the mean and standard deviation, median and interquartile range, quantity and percentage, and frequency, depending on the distribution and type of data. This encompasses participant demographics as well as adherence to exercise. To evaluate the normality of the data, we will examine the skewness and kurtosis statistics (the ratio of the statistic to the standard error) by conducting the Shapiro-Wilk test. Boxplots are employed to detect outliers.

The main outcome measure, the mean changes in hamstring isometric peak force between 4 and 12 weeks, will be assessed using a paired t-test. The main hypothesis will be tested by comparing the changes in the mean difference between the intervention group and the standard

care group. The missing data will be analysed according to the intention-to-treat concept, considering the groups to which participants have been randomly allocated. Descriptive analysis, on the other hand, will describe missing data patterns in great detail to look for possible biases. If the data distribution exhibits non-normality or ceiling/floor effects, a non-parametric test (specifically, the Mann-Whitney test) will be conducted. Furthermore, this study will employ one-way repeated-measures ANOVA within-group measurements to investigate potential differences between the Quadriceps Index and Hamstring Index over an interval of time.

The secondary outcome data, which includes measurements of hamstring flexibility, range of motion, IKDC scores, and exercise adherence, will be summarised and evaluated in a manner consistent with the primary result. A repeated measures analysis of variance (ANOVA) will be used to examine the impact of rehabilitation and time on all the measured variables.

Statistical significance will be determined by a p-value of less than 0.05 (two-tailed) for all conducted tests with a 95% confidence interval.

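### The week-4 starting value of the primary change score may be measured after ULIT has begun, which would subtract part of any effect

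*Protocol*

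**What the plan says.** Four parts of the protocol bear on this.

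- **Outcome.** The Statistical Analysis section defines the main measure as "the mean changes in hamstring isometric peak force between 4 and 12 weeks". The main hypothesis is then tested by comparing that change between the two groups.
- **Start of treatment.** The section on the intervention group says: "In the fourth week following ACLR surgery, the treating physiotherapist will conduct the ULIT as a single, personalised session". Participants are then told to do the exercises every day for eight weeks, from week 4 to week 12.
- **Timing of the test.** Data Collection refers to "The subsequent assessment in the 4th week" and gives it, like the later visits, a window of 14 days either side.
- **Baseline and allocation.** Data Collection says: "Baseline evaluations will be conducted throughout the pre-operative period, within a range of 14 days". Under Randomisation and Allocation, the envelope is opened after that first test (T1). Preoperative strength is therefore known before allocation, but the Statistical Analysis section does not use it as the start of the primary change.

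The Research Hypothesis concerns strength at 12 weeks.

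**The concern.** A change score measures a treatment effect cleanly when its starting value is free of treatment. Here the first ULIT session and the week-4 test are planned for about the same time. The test window extends two weeks past day 28, and the visible text does not say which comes first. In the ULIT arm, any strength gained between the first session and a late test enters the starting value and is then subtracted from the result. Controls have no such gain to lose, so the difference between groups shrinks.

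The risk is a missed effect rather than a false positive. That matters in a trial of 14 evaluable participants per arm, planned for 80% power. Once the data are collected, no analysis of the week-4 change can recover a pre-treatment value that was never taken.

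**Working it through.** **Inputs from the protocol.** First ULIT session in the fourth week, taken as days 22 to 28. Week-4 test at day 28 ± 14. Programme of eight weeks = 56 days. SD 0.71, two-sided alpha 0.05, power 80%, 14 per group, raised to 16 for 10% attrition (Sample Size and Statistical Analysis).

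**The plan's own figure.** The attrition step reproduces: 14 / 0.9 = 15.6, rounded up to 16. The 14 does not, because Sample Size gives no target difference. Solving backwards for a two-group comparison:

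- normal approximation: 0.71 × (1.96 + 0.84) × √(2/14) = 0.75
- t-based: 0.78, that is d = 0.78 / 0.71 = 1.10

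The d of 1.10 is therefore an inference. The figure of 14 also fits a paired within-group calculation: (0.71 × 2.80 / 0.55)² = 13.1, rounded up to 14, where 0.55 = 1.55 − 1.0 is the involved-limb change in Table 1.

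**Exposure before the latest permitted test.** The window runs from day 14 to day 42.

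- Start at day 28: 42 − 28 = 14 days; 14/56 = 25%.
- Start at day 22: 42 − 22 = 20 days; 20/56 = 36%. If a day-22 starter continues to day 84, the programme lasts 62 days and the share is 20/62 = 32%.

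**Average exposure.** Assume test days are spread evenly over the 28-day window. Tests before the first session lose nothing. For a start at day s, the mean number of ULIT days before the test is (42 − s)² / (2 × 28).

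- s = 28: 196/56 = 3.5 days; 3.5/56 = 6%.
- s = 22: 400/56 = 7.1 days; 7.1/56 = 13% (7.1/62 = 12% on the longer programme).

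**Effect on power.** Assume the effect builds linearly with exposure and the SD is unchanged. Two-sample t-test, d = 1.10 × (1 − loss):

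| Loss | d | Power, 14 per arm | Power, 16 per arm |
|---|---|---|---|
| 0 | 1.10 | 80% | 85% |
| 6% (even spread, start day 28) | 1.03 | 75% | 81% |
| 13% (even spread, start day 22) | 0.96 | 69% | 75% |
| 25% (all tested day 42, start day 28) | 0.83 | 56% | 62% |
| 36% (all tested day 42, start day 22) | 0.71 | 44% | 49% |

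The last two rows need every participant to be tested on the last permitted day. They are outer bounds, not expectations.

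**The case against.** The strongest reply is that a week-4 start is sensible. Both arms are planned to have the same standard care until ULIT begins, so a value taken just before the first session is the last untreated measurement after surgery and graft harvest. That stands: being measured after allocation does not by itself bias the value. A reader might infer that any post-randomisation starting value invalidates the comparison, but the documents do not support that. The problem is confined to tests that follow the first session.

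The order may also be given somewhere not available here. The flow chart (Figure 9), the data-collection table (Table 3) and Appendix I are not shown, and the Data Collection text breaks off before the strength-testing description resumes. This limits confidence to moderate. If one of those places fixes the order, the point reduces to cross-referencing it and closing the late side of the window.

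The power figures rest on assumptions, and a repeated-measures ANOVA is also planned, so the week-4 change is not the only analysis. Both remarks are fair, but neither alters how the primary measure is defined.

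Three further inferences are tempting and should not be drawn.

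- *Test timing differs between arms.* The windows are the same for both groups and blinded assessors do the testing at a separate clinic. No mechanism is stated, so loose windows chiefly add noise.
- *Objective 1 is wrong to list week 4.* It names comparison times ("compared to the standard care alone group at 4, 8, and 12 weeks post-ACLR"), and a week-4 comparison can serve as a check of comparability.
- *Anyone who misses week 4 has no primary outcome.* That presumes complete-case handling. The protocol commits to intention-to-treat, and a statistical analysis plan may settle the details.

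**Conclusion.** The point holds with moderate confidence. As the visible text stands, a test at day 42 is within protocol and follows 14 to 20 days of daily ULIT, yet counts as the starting value of the primary change. If ULIT has an effect by then, the estimate is biased toward no difference.

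The size is not knowable from the document. With linear build-up, an individual tested at day 42 loses about 25% to 36% of the effect. The average loss is about 6% to 13% with evenly spread test days, which puts power at about 69% to 75% with 14 per arm or 75% to 81% with 16. A reader might take the 44% to 56% figures as the expected power at 14 per arm. They are not: they need every test on the last permitted day, on top of the linear assumption and a back-solved d of 1.10.

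**What to change.** Reconcile the intervention, Data Collection and Statistical Analysis sections in one of two ways.

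1. **Keep the week-4 start.** State that the week-4 strength test is done before the first ULIT session (test, then train, at the same visit if convenient). Close its window at that session, and test controls at the same post-operative time so that the tighter rule does not itself create a timing difference. The cost is slightly tighter scheduling, with no new visit.
2. **Use the preoperative value.** Make the primary comparison week-12 strength between groups, adjusted for strength at T1. This uses data already collected, matches the stated hypothesis and keeps the baseline before randomisation. The cost is that preoperative strength may correlate less with week-12 strength than a week-4 value would, giving up some precision.

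Moving allocation to after the week-4 test is optional. Neither remedy requires it. Whichever is chosen, the change should be made before recruitment, because the order of test and session cannot be repaired afterwards.

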### **Intervention Fidelity**

A physiotherapist will conduct follow-up phone calls to evaluate exercise adherence for both groups. They will use standardized guidelines and handouts to encourage patients' exercise adherence, minimizing biases. A flexible and patient-centred approach is applied to address a patient's deviation from their rehabilitation protocol. This involves assessing and reevaluating the patient's progress, modifying the rehab plan for individual needs, rescheduling missed sessions, maintaining weekly communication (online exercise diary), documenting changes and analysing data under an intention-to-treat (ITT) protocol to reduce bias and preserve randomisation.

### **Blinding**

The individuals responsible for evaluating the results and managing the data are unaware of the assigned therapy. Participants will be informed that they will be assigned randomly to either the standard care group or the intervention group. The patients are reminded not to reveal their group allocation to the physician or medical officer who performed the outcome assessment. The details of ULIT are not recorded in the medical record. A sports physician and medical officer, who is blinded to the group allocation and located away from the physiotherapy outpatient unit, will assess all outcome measures at the Orthopaedic Clinic. If any participant notifies the assessor about their post-operative training session, this information will be

recorded and reported. The rationale for this notification will be documented when the randomization is revealed. An intention-to-treat analysis will be conducted.

Due to the nature of the treatments, it will not be possible for physiotherapists to be blinded to the treatment allocation of patients. The primary investigator (PI) and data analyst (not from the same departments) will be unaware of the treatment allocation as data will be evaluated using coded identification numbers. The central study coordinator (a staff who is not involved in intervention and outcome assessment) will be responsible for coding and re-coding the identification numbers.

A half-day training workshop for blinded assessors and treating physiotherapists will be conducted before this study commences to enhance data quality and protocol adherence, reduce the bias risk of assessment and treatment, and increase the confidence and competence of the investigator.

To assure the overall standard and credibility of this clinical study, the process of disclosing the assigned treatment to participants will only be done in exceptional instances, for instance when there is a risk of harm, and when knowing the real treatment becomes essential for the participant's ongoing care. Before disclosing the group allocation, the PI will determine the necessity and amount of un-blinding. The allocation will remain confidential and will not be revealed to other study team members. If any code breaks occur, the PI will report it with the justifications.

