## **Research Objective**

The main objective of this study is to investigate the effects of upper limb isometric training (ULIT) combined with standard care rehabilitation versus standard care rehabilitation alone on hamstring strength and physical function in early phase postoperative ACLR patients.

The secondary objectives are:

- 1) to assess the efficacy of ULIT compared to standard care in improving physical function three months after surgery.
- 2) to explore ULIT's effectiveness in enhancing hamstring flexibility at three months following ACLR
- 3) to assess patient adherence to ULIT.

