### **Adherence monitoring**

A threshold for adherence is established for the experimental group, targeting participants to report a self-perceived rating of  $\geq 80\%$  (Cimino & Braun, 2023). Participants are advised to adhere to the instructions on home-based programs included in their respective flyers. The study used self-report scales and exercise diaries to measure adherence to the home exercise programme over 3 months. Participants are classified as adhered ( $\geq 3$  times per week) or non-adhered ( $\leq 2$  times per week) based on the average frequency of sessions performed weekly (Welling, 2024). Participants are instructed to complete the weekly exercise diary via online Google Form (see Appendix J). Physiotherapists will contact participants weekly via phone or WhatsApp to reinforce their exercise adherence. Self-report questionnaires and activity diaries have demonstrated efficacy, simplicity, and affordability as means of assessing exercise adherence in clinical and research contexts (Lahham et al., 2018; Nicolson et al., 2018).

The Sports Injury Rehabilitation Adherence Scale (SIRAS) is administered by a physician and physiotherapist to assess the level of adherence of all patients to the rehabilitation procedure in both study groups at the Orthopaedic Clinic and physiotherapy outpatient rehabilitation session (see Appendix E). The SIRAS is a reliable measure for evaluating clinic-based adherence in musculoskeletal rehabilitation with inter-rater and test-retest reliability coefficients ranging from 0.76 to 0.93 (Furlong & Hall, 2023).

ACL rehabilitation adherence and recovery can be significantly impacted by fear of movement, addressed by the Tampa Scale of Kinesophobia (TSK), a self-report checklist, utilising a 4-point likert scale (Ohji et al., 2022). By monitoring this fear, clinicians can improve compliance and modify rehabilitation programs (Kasmi et al., 2023). The TSK enables personalised treatment to overcome physical and psychological barriers. The TSK will be assessed preoperatively and at 3 months post-ACL reconstruction to monitor changes in fear of movement and reinjury (see Appendix F). The Tampa Scale of Kinesophobia (TSK) is available online for free use at <https://eprovide.mapi-trust.org/instruments/tampa-scale-for-kinesiophobia-11>, requiring only proper citation and acknowledgement in relevant publications or research (Woby et al., 2005).

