## Data Management and Confidentiality

Only the supervisor, Principal Investigator (PI), co-researcher, and independent statistician have the right to access the data, and it will not be disclosed to any non-relevant party. The researcher supervisor and the PI will provide advisory support to the trial investigators in monitoring withdrawals, assessing ethical conduct, addressing missing data and reviewing major adverse events. A case report form (CRF) will record instances of unavailable data, ensuring uniformity and precision, and providing essential information for analysis and management. The data will be stored in a secure cabinet in the office of the PI and will be preserved for at least 5 years after the study is finished and published.

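### Coding alone does not secure the stated blinding of the PI and data analyst, because Specific Objective 4 needs adherence data that apply to the ULIT arm only

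*Protocol*

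**What the plan says.** **The blinding claim.** The protocol makes it twice. Under Blinding, the PI and data analyst "will be unaware of the treatment allocation as data will be evaluated using coded identification numbers", and a central study coordinator with no part in intervention or assessment "will be responsible for coding and re-coding the identification numbers". Under Randomisation and Allocation, analysis works from allocation codes, "ensuring that the data analyzers remain unaware of the study group allocation".

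**The adherence objectives.** Research Objective lists as a secondary aim "to assess patient adherence to ULIT". Specific Objective 4 is to analyse the "relationship between patient adherence to ULIT and improvements in hamstring strength and physical function". Under Adherence monitoring, "A threshold for adherence is established for the experimental group", at 80% or more. Statistical Analysis counts exercise adherence among the secondary outcome data.

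**Data access.** Data Management and Confidentiality states: "Only the supervisor, Principal Investigator (PI), co-researcher, and independent statistician have the right to access the data". It keeps the data in the PI's office and gives the PI an advisory role on missing data. It does not distinguish types of data or say when each may be opened.

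**The concern.** A code hides allocation only while nothing attached to it differs by design between the arms. Adherence to ULIT does differ by design: a control patient has no ULIT to adhere to. An analyst who holds such a variable, or who is told which group to use for Objective 4, knows what the code means.

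This matters because some decisions remain open once data are in hand. Statistical Analysis uses boxplots to find outliers but does not say what is done with them. It refers missing data to the intention-to-treat concept and to a description of patterns, without a handling method. Data Collection records both the mean and the best of the repeated contractions. The text ties the average to the limb-symmetry indices, but does not say which value enters the primary change in hamstring peak force. Those details may properly sit in a SAP. They are relevant here because analyst blinding is the protection the protocol offers while such choices are made, and with 16 patients planned per arm a single excluded value can carry weight.

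**Working it through.** No arithmetic beyond a count applies. The check sets the sections side by side.

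1. **Mechanism of blinding.** Blinding and Randomisation and Allocation give one mechanism for the PI and analyst: coded numbers and allocation codes. Neither section mentions withholding any variable.

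2. **Who can have ULIT adherence.** Under Intervention Group and Control group, only the intervention arm is taught ULIT. Adherence to it is therefore defined in one arm.

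3. **What Objective 4 requires.** To relate ULIT adherence to outcomes, the analyst needs either a ULIT adherence variable, which can be meaningful under one code only, or general exercise adherence together with the knowledge of which code is ULIT. Both routes reveal the code.

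4. **Extent once revealed.** There are two arms in a 1:1 ratio, 16 + 16 = 32 patients. Identifying one group code identifies the other by elimination. This is conditional on the link in step 3 being made.

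5. **Whether the link is kept away from the primary analysis.** Data Management and Confidentiality grants access without limit by data type or time. Statistical Analysis says secondary data, adherence included, are evaluated consistently with the primary result, but gives no sequence. No section holds adherence data back, and none says they are merged early.

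6. **What the described instruments show.** Follow-up calls cover both groups (Intervention Fidelity). The Sports Injury Rehabilitation Adherence Scale covers both groups (Adherence monitoring). For the diary, "Participants are instructed to complete the weekly exercise diary via online Google Form"; it measures the home exercise programme, with a class of at least 3 versus at most 2 times per week, and is not described as ULIT-specific. The form itself is in an appendix that is not shown. These measures need not identify an arm on their own.

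7. **The PI's separate exposure.** Under Adverse events, the questionnaire is part of the training diary, events reach the PI daily, and participants may contact the PI. Under Blinding, the PI also rules on un-blinding. These routes may disclose allocation whatever is done with adherence data.

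Steps 1 to 5 show a stated protection that the stated mechanism does not guarantee. Step 6 limits how far the document proves a breach. Step 7 shows that the PI part of the claim is the weaker one.

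**The case against.** The strongest reply has four parts.

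- **Coding can work.** If the primary comparison is finished before any ULIT adherence is opened, the codes protect it. The protocol does not exclude that order, and the coordinator is well placed to enforce it. This stands. A reader might infer that blinding is impossible under this plan; the document does not support that.

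- **No ULIT-only data field is described.** The calls and the adherence scale cover both groups, and the diary is not described as ULIT-specific. This also stands. A reader might infer that the dataset visibly holds ULIT entries under one code and that all 32 patients are therefore identifiable. That would require ULIT fields to exist and to be merged before the primary analysis, and neither is documented. What remains is that Objective 4 cannot be met without ULIT-arm information.

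- **Order of analysis and staged release belong in a SAP.** In part, yes; silence on sequence alone would not be a finding. The point here is different: the protocol asserts that analysts remain unaware as a result of coding, while its own objectives and access rule leave that unsupported. If a SAP already fixes the order, the protocol wording only needs to refer to it.

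- **The consequence is small.** Study Design calls the trial single-blinded at the assessor, and blinded assessors away from the physiotherapy unit measure the outcomes. Knowing the codes cannot change a recorded force. The switch to a Mann-Whitney test under non-normality is also stated in advance, and boxplots are said only to detect outliers, not to exclude them. This confines the risk to the analysis stage but does not remove it, since missing-data handling, the treatment of outliers and the choice of peak-force score remain open in this document.

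**Conclusion.** The point holds in a limited form: the protocol's claim that the PI and analyst stay unaware of allocation is not secured by coding alone, given Objective 4, the experimental-group threshold and unrestricted data access.

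It rests on two assumptions: that Objective 4 is carried out as written, and that no unseen document already sets the order of release. The effect is limited to analysis-stage decisions. No figure in the document allows the possible bias to be sized, and it should not be read as evidence that the result will be biased or that unblinding will occur.

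For the PI, separating adherence data would not be enough, because adverse-event reports and direct contact with participants may reveal allocation anyway. A reader might infer that the PI should be barred from the diaries. The document does not support that, since adverse events are collected there and go to the PI daily. The change is worth making because it is nearly free.

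**What to change.** Add a data-release rule to the Blinding section, run by the central study coordinator already named there.

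1. **First release.** Strength, flexibility and IKDC data, with the reasons for missing data, under neutral group codes and with any mention of ULIT removed. The analyst fixes the analysis sets, the peak-force score and the handling of outliers and missing data, then saves the primary result.
2. **Second release, only after that.** ULIT-specific adherence and fidelity data, for Objective 4.

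Leave adverse-event reporting to the PI as it is. Because that route may reveal allocation, narrow the blinding statement to the data analyst for the primary analysis, and align the matching sentence under Randomisation and Allocation and the access statement under Data Management and Confidentiality.

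The coordinator role already exists, so no new post is needed. The cost is the coordinator's effort in preparing two extracts, a short delay to the adherence analysis, and a less favourable blinding statement for the PI.
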